## Abstract

**Background:**

Glaucoma stands as a prominent global cause of irreversible blindness and the primary treatment approach involves reducing intraocular pressure (IOP). However, around one-third of patients exhibit disease progression despite effective IOP reduction. Microvascular endothelial function, chronic inflammation, and oxidative stress are known to affect retinal neuronal networks and have been associated with disease severity and progression. Exercise training has the potential to counteract these mechanisms as add-on treatment to usual care.

**Aims:**

The HIT-GLAUCOMA study will investigate the effects of a 6-month high-intensity interval training (HIIT) on intermediate endpoints such as local retinal microvascular and systemic large artery function, inflammation, and oxidative stress as well as clinical endpoints such as visual field indices, optic nerve rim assessment, retinal nerve fiber layer thickness, IOP, number of eye drops, vision-related quality of life and ocular surface disease symptomatology.

**Methods:**

The study is a multi-center randomized controlled clinical trial in patients with both normal tension and high-tension primary open angle glaucoma. Across two study centers, 128 patients will be enrolled and randomized on a 1:1 basis into an exercise intervention group and a usual care control group. The primary microvascular endpoints are retinal arteriolar and venular flicker light-induced dilation at 6 months. The primary endpoint in the systemic circulation is brachial artery flow-mediated dilation at 6 months.

**Anticipated results:**

We hypothesize that exercise therapy will improve retinal microvascular function and thus ocular blood flow in patients with glaucoma. As clinical outcomes, we will investigate the effect of exercise on visual field indices, optic nerve rim assessment, retinal nerve fiber layer thickness, IOP, number of eye drops, vision-related quality of life and ocular surface disease symptomatology.

**Discussion:**

HIT-GLAUCOMA is a blueprint trial design to study the effect of exercise training on neurodegenerative and cardiovascular diseases. Importantly, patients are also expected to benefit from improvements in general health and cardiovascular co-morbidities. If proven effective, exercise may offer a new add-on treatment strategy to slow glaucoma progression.

**Clinical Trial Registration Number:**

The trial is registered at Clinicaltrials.gov under the identifier NCT06058598 and is currently in the recruitment stage.

## Introduction

### Glaucoma and cardiovascular risk

Glaucoma is an optic neuropathy characterized by degeneration of retinal ganglion cells, thinning of the retinal nerve fiber layers, and cupping of the optic disc (Jonas et al., 2017). Primary open angle glaucoma (POAG) can be sub-classified according to the maximal intraocular pressure (IOP). This arbitrary classification with a cut-off at 21 mmHg IOP stratifies POAG patients into high-tension glaucoma (HTG) and normal tension glaucoma (NTG) (BMJ Publishing Group Ltd, 2021). It is hypothesized that impaired ocular perfusion pressure, impaired microvascular endothelial function and increased oxidative stress are additional disease drivers (Chu-Tan et al., 2022; Benoist d Azy et al., 2016; Melgarejo et al., 2023). The glaucomatous changes lead to a loss of visual field (Venkataraman et al., 2010; Quigley, 2011), and in around 15%–20% of glaucoma cases the disease progresses to blindness (Susanna et al., 2015). Glaucoma has become the global leading cause of irreversible blindness (Topouzis et al., 2007). It affects over 80 million people worldwide (Topouzis et al., 2007) and the prevalence is estimated to increase to 111 million in 2040, in accordance to population ageing (Tham et al., 2014). The main goal of glaucoma treatment is to lower IOP. However, at least one-third of patients show disease progression despite IOP lowering (Peters et al., 2014; Susanna et al., 2015).

Some subclinical pathophysiological features of cardiovascular diseases (CVD) overlap with glaucoma, suggesting an association between CVD and glaucoma (Choi et al., 2023). A growing body of evidence indicates that glaucoma is associated with many systemic CV risk factors such as obesity, hypertension, active smoking status, low high-density-lipoprotein (HDL), high low-density-lipoprotein (LDL) levels and hypertriglyceridemia (Lin et al., 2010; Kreft et al., 2019; Talaat et al., 2021; Wändell et al., 2022). Primary and secondary vascular dysregulations have previously been hypothesized as components of the etiology of glaucoma (Flammer and Konieczka, 2017). Earlier research demonstrated that systemic comorbidities associated with endothelial lesions, atherosclerosis and hypoperfusion may lead to damage of the retinal nerve fiber layer and the underlying connective tissue (Dascalu et al., 2021). Several studies have shown both hypertension, nocturnal hypotension and daytime blood pressure variability to be common CV risk factors for progression (Dascalu et al., 2021; Van Eijgen et al., 2023). Glaucoma may therefore be considered as an independent risk predictor of new-onset CVD (Choi et al., 2023), and *vice versa*. Conversely, glaucoma patients with healthy lifestyle behaviors have shown a reduced risk for incident CVD compared to those with unhealthy behaviors (Choi et al., 2023). Thus, the importance of vascular and other non-IOP related risk factors underscore the need for screening of alternative biomarkers of glaucoma and by extension CV comorbidities.

To date, research on the association of glaucoma disease with large artery structure and function in the systemic circulation is scarce. Since patients with glaucoma suffer from CV co-morbidities and present with systemic inflammation and oxidative stress, they are prone to develop large artery endothelial dysfunction and unfavorable arterial stiffness. A holistic approach including the assessment of brachial artery flow-mediated dilation (FMD) and pulse wave velocity (PWV), both being large artery surrogate markers for CV risk (Vlachopoulos et al., 2010; Thijssen et al., 2011), may provide a more thorough understanding of the bidirectional relation between systemic vascular disease and local neurodegenerative eye disease.

### Glaucoma and the retinal microcirculation

The blood flow in the retina maintains a constant perfusion level through the intricate interplay between neurovascular coupling, myogenic responses, flow-mediated mechanisms, and metabolic processes, facilitated by the release of vasoactive substances from the endothelium and retinal tissue (Koller and Toth, 2012). The capillary endothelial cells and the vascular smooth muscle cells are responsible for the pressure-dependent myogenic constriction (Bayliss-effect) and flow-dependent nitric oxide (NO)-induced dilation by means of shear stress (Hanssen et al., 2022). In addition, endothelin-1 (ET-1) has been suggested to play an important role in the maintenance and regulation of local blood flow (Palmer et al., 1988; Moncada and Higgs, 1993). Together with NO, ET-1 ensures a balance between vasoconstrictive and vasodilatory capacities of the endothelium (Koller and Toth, 2012).

Local oxidative stress has been acknowledged as a factor in POAG pathogenesis for over 30 years. Since then, several studies have supported the role of free radical-induced oxidative stress in trabecular meshwork (TM) cell loss (Zhou et al., 1999). The retina is consistently exposed to reactive oxygen species (ROS) (Nita and Grzybowski, 2016). An imbalance between ROS production and antioxidant defenses can lead to cellular damage and apoptosis (Chrysostomou et al., 2013; Pinazo-Durán et al., 2015). Elevated IOP and visual field damage have been linked to oxidative DNA damage affecting TM cells (Saccà et al., 2005; Nita and Grzybowski, 2016). In addition, neurotrophic factors (NTFs), in particular brain-derived neurotrophic factor (BDNF), have been identified in the pathogenesis of glaucoma (Lambuk et al., 2022). BDNF is locally regulated in the retina and transported from the brain to the retina through retrograde transport (Lambuk et al., 2022). Disruptions in the retrograde transport and reduced levels of BDNF in the serum and ocular fluids of patients with glaucoma suggest that neurotrophic deprivation contributes to glaucomatous optic neuropathy (Lambuk et al., 2022).

Retinal microvascular endothelial dysfunction is a key predictive vascular parameter, along with arterial blood pressure and vascular rarefaction (Gugleta et al., 2012; Wang et al., 2015; Kwon et al., 2017). Associations of retinal vessel diameters and function with CV risk and disease have previously been extensively reviewed (Hanssen et al., 2022). Narrowing of the central retinal arteriolar diameter equivalent (CRAE), widening of central retinal venular diameter equivalent (CRVE), and a lowering of arteriolar-to-venular diameter ratio (AVR) associate with an increased risk of CVD and CV mortality (Green and Smith, 2018; Vera et al., 2019). A similar retinal vessel diameter constellation was found in POAG patients when compared to healthy subjects (Chiquet et al., 2020). Moreover, impaired retinal flicker-induced dilation (FID) correlates with increased CV risk in diabetes (Valenzuela et al., 2023), hyperglycemia (Green and Smith, 2018), hypertension (Vera et al., 2019), dyslipidemia (Karakucuk et al., 2020), obesity (Kaminsky et al., 2013), coronary artery disease (Ramos et al., 2015), and chronic kidney disease (Whyte et al., 2013). Blood flow alterations in the optic nerve head (ONH) have been identified as a significant risk for development and progression of glaucoma, highlighting the importance of the vascular system’s responsiveness to metabolic changes for disease progression (Flammer et al., 2002).

### Exercise treatment in patients with glaucoma

Regular physical activity and exercise could potentially reduce the main underlying mechanisms in the development and progression of CVD, such as inflammation, oxidative stress and endothelial dysfunction (Green et al., 2017; Valenzuela et al., 2023). The effects of exercise training are mediated through a repeated hemodynamic stimulation occurring during each bout of exercise. This stimulation leads to an increase in the production and bioavailability of endothelium-derived substances such as NO. Regular bouts of exercise can induce functional and structural vascular adaptations that improve systemic and local blood flow as well as oxygen supply (Green and Smith, 2018). Additionally, HIIT temporarily reduces IOP values in physically active young subjects (Vera et al., 2019; Karakucuk et al., 2020).

Cardiorespiratory fitness inversely correlates with CV mortality and morbidity (Kaminsky et al., 2013). High-intensity interval training (HIIT) appears to be the most promising candidate to increase this fitness and vascular health (Wisløff et al., 2009; Whyte et al., 2013; Ramos et al., 2015). Furthermore, emerging evidence indicates that HIIT effectively reduces oxidative stress and increases the bioavailability of NO (Areas et al., 2019). When compared to low-to-moderate intensities, exercising in intervals and at higher intensities has been shown to be superior in improving insulin sensitivity, glucose metabolism, HDL and LDL, left ventricular dysfunction, NO bioavailability, endothelial function, as well as cardiorespiratory fitness (Tjønna et al., 2008; Wisløff et al., 2009; Whyte et al., 2013; Weston et al., 2014; Ramos et al., 2015; Streese et al., 2018). Substantial evidence suggests that not only local, but also systemic vascular abnormalities play an important role in the pathophysiology of glaucoma (Bonomi et al., 2000; Dascalu et al., 2021). In glaucoma patients, dynamic exercise such as jogging and cycling has been shown to lower IOP, with longer and more intense training having greater effects (Streese et al., 2018). Exercise also demonstrated to induce higher levels of BDNF and improve mitochondrial function (Zhu et al., 2018; Chu-Tan et al., 2022). Notably, having patients with glaucoma adopting an active lifestyle is beneficiary for their general health, and concomitant management of CV risk factors is an effective means to improve CV health and quality of life.

## Methods and analysis

The long-term clinical goal of HIT-GLAUCOMA is to slow glaucoma progression through an exercise intervention. This trial will investigate the effects of HIIT on retinal microvascular structure and function, systemic large artery health as well as systemic inflammation and oxidative stress in patients with glaucoma. These mechanisms represent the intermediate endpoints and are known to influence glaucoma progression.

### Objectives and outcome measures

#### Primary

• Retinal microvasculature (local): the primary objective in the retinal microcirculation is to examine the effects of a 6-month HIIT-intervention on maximal flicker light-induced retinal arteriolar (aFID) and venular (vFID) dilation as a marker of microvascular endothelial function in patients with glaucoma. We hypothesize that exercise treatment significantly increases retinal aFID and vFID when compared to the control group.

Large arteries (systemic): the primary objective in the macrocirculation is to examine the effects of a 6-month HIIT-intervention on FMD as a marker of large artery endothelial function in patients with glaucoma. We hypothesize that exercise treatment significantly increases FMD as compared to the control group.

#### Secondary

• To investigate whether 6 months of exercise training improve CRAE and CRVE diameters in glaucoma patients compared to the control group.• To investigate whether 6 months of exercise training improves PWV as a marker of large artery stiffness in glaucoma patients compared to the control group.• To investigate retinal aFID and vFID, other flicker light derived markers, as well as retinal CRAE and CRVE after 6 months of exercise training and a further 6 months of self-maintenance exercise training as compared to the control group at 12 months.• To investigate large artery FMD and PWV after 6 months of exercise training and a further 6 months of self-maintenance exercise training as compared to the control group at 12 months.• To investigate whether 6 months of exercise training increase brain-derived neurotrophic factor (BDNF) levels and reduce inflammation as well as oxidative stress in peripheral blood. To assess IOP, use of IOP lowering eye drops and occurrence of laser trabeculoplasty or surgical interventions after six and 12 months in the intervention group as compared to the control group.• To assess Optical Coherence Tomography (OCT) and visual field metrics at six and 12 months in the intervention group as compared to the control group.• To assess peak aerobic capacity (VO_2_peak) and objectively measured physical activity at six and 12 months in the intervention group as compared to the control group.• To compare changes in 24 h ambulatory blood pressure measurement and blood pressure variability at six and 12 months in the intervention group and the control group.• To compare changes in vision-related quality of life at six and 12 months in the intervention group and the control group.• To compare changes in questionnaire-derived ocular surface disease index and dry eye disease symptoms in the intervention group and the control group.

### Study design

The HIT-GLAUCOMA study is a multi-center, prospective, randomized controlled, clinical intervention study. Two centers are involved: The University of Basel (Switzerland) comprised of the Department of Sport, Exercise and Health (DSBG) and the Department of Ophthalmology, and the University of Leuven (KU Leuven, Belgium), comprised of the Department of Ophthalmology, the Department of Neurosciences and the Department of Rehabilitation Sciences. In Basel, the clinical ophthalmological examination will be carried out during the glaucoma consultation at the University Eye Clinic, while retinal vessel analyses, systemic vascular diagnostics and further analysis including cardiopulmonary exercise testing (CPET) and exercise training will be performed at the DSBG. In Leuven, clinical ophthalmological assessments, retinal vessel analyses and further analyses will be performed during the glaucoma consultation at the University Eye Clinic (UZ Leuven, Belgium), while systemic vascular diagnostics and CPET as well as exercise training will be performed at the Department of Rehabilitation Sciences.

In the HIT-GLAUCOMA study, the effects of a 6-month exercise intervention in patients with glaucoma (*n* = 64) are compared to a control group of glaucoma patients (*n* = 64) who receive guideline-based physical activity recommendations (150–300 min of moderate-intensity aerobic physical activity, or 75–150 min of vigorous-intensity activity, or equivalent combination of both throughout the week), while accounting for concomitant changes in glaucoma standard-of-care medication. Patients with NTG and HTG will be randomized into two groups (Figure 1): the intervention group (HIIT; *n* = 32 per center) will take part in a combined and progressive moderate continuous training (MCT) and HIIT; the control group (CG; *n* = 32 per center) will receive physical activity recommendations as control condition. Exercise training is offered as adjunct treatment to the standard of care. The supervised exercise intervention will terminate after 6 months followed by 6 months of unsupervised self-maintenance exercise training or control condition.

**FIGURE 1 F1:**
[figure not shown]
Trial flow chart.

### Selection of subjects

#### Inclusion criteria

Patients eligible for inclusion must meet all of the following criteria: age 40–80 years; diagnosed with POAG (both NTG and HTG); being in regular follow-up in either of the two study centers and having signed written informed consent.

#### Exclusion criteria

Patients eligible for this study must not meet any of the following criteria: having had glaucoma surgery within 6 months before start of the project; changes in topical medication or laser trabeculoplasty within 3 months before start of the project; severe glaucoma (visual field mean deviation lower than −12Db); eye disease that has a significant impact on the visual field; life-threatening arrhythmia, aberrant CPET (e.g., signs of ischemia) which precludes participation in an exercise trial; insulin-treated diabetes, chronic obstructive pulmonary disease or cancer; mental, clinical or physical limitation precluding safe participation in a high intensity exercise program. Subjects that perform more than 150 min of moderate to vigorous physical activity per week as defined by the Physical Activity Vital Sign questionnaire are also excluded (Kuntz et al., 2021). All participants considered for study participation, per the above criteria, will be documented on the Screening Log, including screening failures.

#### Recruitment and randomization

Eligible glaucoma patients will invited to participate during their routine glaucoma consultation at the Eye Clinic of the University Hospital Basel or the Glaucoma Clinic of the University Hospitals UZ Leuven. Overall, 128 patients will be enrolled: 64 POAG (HTG and NTG) patients in Basel and 64 in Leuven.

Participants will be randomized to either HIIT or CG, stratified for the study site. Randomization is carried out via Redcap^®^ to ensure concealed allocation and minimize selection bias. Block randomization will be performed (blocks 4–6) via Redcap^®^. Patients will receive a unique identification number, which will be used on all subsequent transcripts, on all collected data and in the Redcap^®^ database instead of the participant´s name to assure pseudonymity of all data on all documents and in all web-based platforms. The following randomization procedures have been established: single blinding of the study personnel involved in the assessments during study visits to avoid motivational bias. Analysis of imaging data will be performed off-line by blinded researchers.

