### Concomitant care

Both intervention and control group will continue to receive all routine medical and pharmacological management.

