### Data analysis

Primary outcome of the study is the effect of 6-month exercise training on maximal aFID and vFID in the HIIT group compared to the control group. Descriptive statistics (mean, standard deviation) will be used to describe baseline and follow-up characteristics. Normal distribution of data will be tested by means of Shapiro-Wilk test. To analyze intervention effects after 6 months, we will use an analysis of covariance (ANCOVA) according to the intention-to-treat principle to compare differences in primary and secondary endpoints between HIIT and control group, corrected for the corresponding baseline value and main confounders. Boxplots will be used to visualize primary and secondary endpoints before and after the 6-months exercise intervention. If the fraction of missing values exceeds 5%, we will account for missing data using multiple imputation. A multiple linear regression model, adjusted for covariables as age and sex, will be used to describe the association between the delta change of retinal microvascular adaptations and the delta change of classical risk factors such as VO_2_peak, BMI, systolic and diastolic BP, fasting glucose, serum lipids, hs-CRP, inflammatory and oxidative stress markers as well as BDNF. Changes in glaucoma therapy may coincide with the course of this project, as the trial does not interfere with routine glaucoma management. Therefore, there is a particular need to correct for therapy changes in the statistical analysis. Any changes in therapy will be included as separate variables. Any step-up of therapy, being either surgery, laser trabeculoplasty or additional drops, will be coded as a binary, summarizing variable (yes/no) and as separate variable (quantifying total number of drops, total number of surgeries). Model assumptions will be checked graphically using residual diagnostic plots. All statistical tests will be two‐sided and the significant level is set to 0.05.

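### Drops, laser and surgery are secondary endpoints that turn on a clinician's decision, but the stated blinding is not extended to whoever makes that decision

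*Protocol article*

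**What the plan says.** The list of secondary objectives includes "To assess IOP, use of IOP lowering eye drops and occurrence of laser trabeculoplasty or surgical interventions after six and 12 months", compared between the intervention and control groups.

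The trial leaves these treatments to usual care. Under Concomitant care: "Both intervention and control group will continue to receive all routine medical and pharmacological management". Under Data analysis: "the trial does not interfere with routine glaucoma management".

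Recruitment and randomization defines the blinding in two parts. The first is "single blinding of the study personnel involved in the assessments during study visits to avoid motivational bias". The second is "Analysis of imaging data will be performed off-line by blinded researchers". The section names no other blinded role.

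Study design says, for Basel, that "the clinical ophthalmological examination will be carried out during the glaucoma consultation at the University Eye Clinic", and it describes a similar arrangement for Leuven. Table 2 lists intraocular pressure under glaucoma standard of care at T0, T2 and T3 within the first year, and the assessments section specifies Goldmann tonometry.

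The introduction states: "In glaucoma patients, dynamic exercise such as jogging and cycling has been shown to lower IOP".

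**The concern.** An IOP reading or a vessel diameter is a measurement, and blinding the person who takes it protects it. Starting a drop, a laser procedure or an operation is a choice, and it is protected only if the person choosing does not know the arm. The stated blinding is defined by the assessment task, and its stated aim is to avoid motivational bias. It does not mention therapy decisions.

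Disclosure is easy. An exercise programme cannot be hidden from the patient, and patients must be in regular follow-up at the same two centres where they are recruited. A clinician who learns that a patient is exercising, and who shares the article's view that exercise lowers IOP, has a reason to wait before stepping up.

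Two results are exposed:
- **Therapy use.** Deferred step-up in the exercise arm would appear as fewer drops, lasers and operations, which looks like a clinical benefit.
- **IOP, indirectly.** The same deferral leaves exercise patients on less IOP-lowering treatment, which pushes their IOP upwards and against the intervention.

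**Working it through.** **Step 1: who is covered, endpoint by endpoint.** The article gives no figure to reproduce here, so the text comes first.

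| Endpoint | What produces it | Covered by the stated blinding? |
|---|---|---|
| aFID, vFID (primary) | Study-visit recording, off-line image analysis | Yes |
| FMD (primary) | Study-visit measurement | Yes |
| IOP reading (secondary) | Tonometry at T0, T2, T3 | Yes, as stated; exposed only through therapy received |
| Drops, laser, surgery (secondary) | Decision in routine care | Not stated |

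The last row is the gap. The decider is covered only if that person is also a blinded assessor. Study design makes this possible, because the eye examination takes place in the glaucoma consultation, but no sentence settles it.

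**Step 2: possible size. All rates are assumed.**

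Inputs:
- 128 randomised 1:1 (Abstract).
- 10% dropout (Sample size calculation, large artery part): 128 × 0.9 / 2 = 57.6 per arm.
- Two-sided 0.05 (Data analysis).
- Assumed: step-up rate p of 10%, 20% or 30%; equal true need in both arms; a fraction d of step-ups deferred in the exercise arm only, with d = 1/4 or 1/2.

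Formula: q = p(1 − d); SE = √[p(1 − p)/n + q(1 − q)/n]; z = (p − q)/SE; probability of a significant result = P(|Z + z| > 1.96), with Z standard normal.

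Example, p = 0.20 and d = 1/4: q = 0.15; SE = √[(0.16 + 0.1275)/57.6] = 0.0706; z = 0.05/0.0706 = 0.708; probability 0.109.

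The same scenarios with Fisher's exact test (58 per arm, summed over all binomial outcomes with p < 0.05):

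| Control v exercise | Normal approximation | Fisher's exact |
|---|---|---|
| 10% v 7.5% | 0.076 | 0.033 |
| 10% v 5% | 0.176 | 0.083 |
| 20% v 15% | 0.109 | 0.068 |
| 20% v 10% | 0.329 | 0.236 |
| 30% v 22.5% | 0.151 | 0.110 |
| 30% v 15% | 0.500 | 0.414 |

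The nominal level is 5%. Fisher's test is conservative with few events: with no deferral it rejects in 2.1%, 2.9% and 3.2% of trials at rates of 10%, 20% and 30%. Its 3.3% in the first row is therefore below 5% but above its own 2.1%.

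**Step 3: indirect effect on IOP.** Suppose each step-up lowers IOP by 3 to 5 mmHg (assumed). The gaps in step-up above run from 2.5 to 15 percentage points. The shift in the between-arm mean is then 0.025 × 3 = 0.075 mmHg at the low end and 0.15 × 5 = 0.75 mmHg at the high end.

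**The case against.** The strongest reply is that the deciding clinician may already be blinded. At both sites the ophthalmic study assessments sit in the glaucoma consultation, and Table 2 files them under standard of care. If the consultation clinician does the assessment, the blinding sentence reaches that person. No passage describes a separate, unblinded decision-maker. Being recruited in the clinic reveals that a patient is in the trial, not which arm. This stands as far as it goes: a reader might infer that the treating ophthalmologist is unblinded, and the article does not say so. It does not say the opposite either, and the sentence is tied to study-visit assessments. Any step-up decided outside those visits is not addressed.

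Three further points deserve a hearing.

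- **Condensed article.** Operational detail on clinic records and unblinding logs may be in the full protocol, so its absence here is not the finding. The finding is that the scope of blinding is stated, and as stated it does not reach a named endpoint.
- **Planned correction for therapy changes.** Data analysis does foresee adjusting for step-up. That may help the IOP comparison, though imperfectly, because step-up occurs after randomisation and could itself reflect knowledge of the arm. It cannot protect step-up as an endpoint.
- **Motive and size.** That clinicians would defer is a plausible inference, not something the documents report. Controls are also advised to be active, which narrows the perceived contrast. Recent therapy changes, recent surgery and severe glaucoma are excluded, so low step-up rates are plausible, and there the exact test gives the smaller figures.

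**Conclusion.** The concern holds in a limited form. A set of secondary endpoints depends on decisions, and the stated blinding is not extended to the decider. Because patients can disclose their arm, those decisions could be affected, and IOP indirectly.

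A reader might go further and conclude that the IOP measurements are biased, that the primary results are at risk, or that no therapy or IOP result could be credited to exercise. The documents do not support this. Assessors and image readers are stated to be blinded, which covers the IOP reading and aFID, vFID and FMD, and the deciding clinician may be among those assessors.

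The size is unknown. The range of about 8% to 50% (normal approximation) or 3% to 41% (Fisher) rests entirely on assumed step-up rates of 10% to 30%, deferral of one in four to one in two, equal true need, and about 58 patients per arm. It shows that a moderate shift in decisions could matter, not that one will occur. The point is worth acting on because the remedy is cheap and reasons for step-up are hard to reconstruct later.

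**What to change.** In Recruitment and randomization, extend the blinding statement to the clinicians who decide on glaucoma therapy. Support it with three measures:

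1. Keep the allocation out of the ophthalmology record.
2. Instruct patients not to reveal their arm at any glaucoma consultation up to T3.
3. Record in the eCRF any unblinding of a deciding clinician and the stated reason for each step-up.

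Where masking fails, report how often and interpret the therapy endpoint with that caution.

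Do not add an analysis that leaves out step-ups decided after unblinding. The feared bias works through step-ups that did not happen, so removing observed ones cannot recover them. If exercise patients disclose more often, it would remove more events from their arm and enlarge a spurious benefit.

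The cost is protocol wording, one patient instruction and one or two eCRF fields, with a small documentation burden. No extra visits or staff are needed and care does not change. Some patients will disclose anyway, so the protection will be incomplete.
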